### Theoretical framework - Behaviour Change Theory

There are a large number of theoretical approaches to behaviour change concentrated in the health psychology literature [41]. Theory-based interventions and detailed descriptions of the behaviour change techniques used in interventions are essential [42]. However, we must be aware when applying psycholgical theories to behaviour change that the determinants of behaviour change are different to the determinants of behaviour so we must focus on predicting and understanding what needs to change and how we can change it instead of simply describing the behaviour or the intention to change [43]. Our lifestyle programme will use the Social Learning Theory as a tool to encourage behaviour change [27]. Social Learning (cognitive) Theory states that we learn behaviours by cognitive and behavioural processes such as reinforcement of positive and negative behaviour [26]. Social Learning (cognitive) Theory outlines the mechanisms through which determinants influence behaviour and thus states how you can change behaviour using them so is deemed suitable for application. The lifestyle programme will use five components of Social Learning Theory to provide women with an opportunity to gain the skills and knowledge needed to improve their lifestyle; self-efficacy, outcome expectancies (beliefs about the outcomes of an alternative behaviour), goal setting, feedback and positive reinforcement (Table 1 outlines the techniques used in the current lifestyle programme study and the link to theoretical framework).

**Table 1 T1:** Behavioural change techniques used in the 10-week lifestyle programme

Component	Objective	Technique
**Psychological variables**		

Self-efficacy	To increase the women's self-efficacy, so they are more motivated to make healthy changes to their lifestyle	Self-efficacy will be increased by: -Problem solving activities in 10-week programme (e.g. minor ailments in pregnancy pass-the-parcel) -Feedback and reinforcement through the group at the 10-week programme -Personal goal setting during 10-week programme - the setting of a realistic and short-term goal will increase experience of success

Outcome expectations	Develop realistic expectations about the benefits of improving their well-being (physical activity, healthy eating and emotional well-being - relaxation)	When setting their personal goal and in the questionnaires, they will be asked to think about the outcomes of any changes to their behaviour and the impact on their lifestyle. The barriers and facilitators of goal attainment will be discussed at the goal setting stage (week 1 of 10-week programme) and goal attainment stage (week 10 of 10-week programme) Baseline questionnaire and goal setting stage (week 1 of 10-week programme) will ask open questions on their expectations and views regarding behaviour change

Feedback	To provide constant feedback to the women throughout the programme to encourage the uptake of healthy behaviours and changes to their lifestyle	Feedback will take the form of changes to their lifestyle as recorded in their diary and involvement in the lifestyle programme (via health care professionals and other women in the group)

Positive reinforcement	Positive reinforcement will be received by women when they engage in healthy behaviours or changes to their lifestyle	Positive reinforcement will be offered to the women to increase their self-efficacy, this will occur through the other women in the group, the health care professionals and self-monitoring of their diary entries

**Social variables**		

Social Support	Support and advice will be received from health care professional and other pregnant women with a BMI of 30 kg/m^2 ^or more	Receive support and advice from Health Care Professionals at the 10-week programme (fitness instructor, Health Psychologist and midwife) Be offered support from other pregnant women with a BMI of 30 kg/m^2 ^or more at the 10-week programme

**Environmental variables**		

Access to health care	Women will be provided with information about other programmes and services that may be of relevance to them during their pregnancy and in the post-partum stage	Women will be provided with information about other programmes and services that may be of relevance to them during their pregnancy (e.g. one session in the 10-week programme is dedicated to signposting to other services). Additional activities (e.g. aquanatal class, supermarket tour and pampering session) will be offered to the women alongside the 10-week programme as taster sessions.

Self-efficacy is central to Social Learning Theory, unless a person believes that they can produce the desired outcomes through the behaviour they have little reason to act. Self-efficacy regulates motivation and determines the goals people set, their determination to meet their goals and the outcomes they expect. Self-efficacy can be increased by four processes. Firstly, if we experience successes then our self-efficacy rises. Each week the women will take part in small problem-solving activities which they can succeed at (e.g. pass-the-parcel game where women had to decide if pregnancy statements were true facts or myths). Secondly, our self-efficacy rises if we see those similar to ourselves succeed; the women will share experiences as a group so that they can share each others experiences and talk about the reasons for their successes and failure (reinforcement and feedback). The third process is through social persuasion, if we are persuaded verbally that we can do something then we are more likely to believe it. To encourage the women, they will receive educational sessions from health care professionals about their health behaviours and their goals for the programme will be discussed with a health psychologist. Finally, our somatic and emotional state influences our self-efficacy; positive mood enhances self-efficacy and makes us view fatigue more favourably. The women will be in the same group for the whole programme so will gain social support and feedback on their behaviour to provide an environment to foster positive mood. Social support has been shown to have a positive impact on our health [44].

The programme will commence with a one-to-one session with a health psychologist to set a personal goal. This will help women to develop a greater feeling of control (self-efficacy) over their behaviour and health and thus empower the women [45]. As stated above, when people have greater levels of self-efficacy they are more likely to engage in certain behaviours. The goal will be broken down into several smaller goals which are easier for the women to achieve, this will be encouraged by following the principles of SMART (specific, measurable, achievable, relevant and timely). It is important at this stage to explore the women's outcome expectations of the behaviour as we must understand the women's attitudes towards their weight and lifestyle if we are to successfully help them to change this behaviour [46]. Therefore, when setting the goal, the women must be encouraged to think about things that will help them to reach these goals and things that will act as a barrier to achieving their goal. They will also be asked to think about previous experiences and why they failed to reach similar goals in the past. The women will be encouraged to self-regulate their behaviour and the attainment of their goals. One reason for this is that people who reward their own achievements achieve more than those who do the same activities without self-rewards. In addition, feedback is vital for the women to change their behaviour [47]. The women will complete a daily dairy (see data collection section for more information). The diary will also act as a behavioural change technique by self-regulation which in turn increases motivation.

### The post-partum programme

Women are reported to be most likely to return to physical activity 4-6 weeks post-partum [48], therefore, women will be invited to a one-off follow up session at this stage. This session will consist of physical activity such as walking with prams and a focus-group to examine their experiences and views of the programme. If women cannot attend this session, they will be provided with information about post-partum physical activity and an individual interview.

### Data Collection and analysis

Mixed-methods of data collection will be employed (Table 2 outlines the data collection and outcome measures); questionnaires including validated measures [31,49-51] and open questions (given out at baseline, the start of the 10-week programme, the end of the 10-week programme and at follow-up), diaries (completed from baseline to follow-up to provide detailed qualitative data) and focus groups at 4-6 weeks post-partum (interviews will be offered where attendance is not possible). The diaries will provide qualitative data daily insight into the women's feelings during pregnancy, behaviour change and any barriers and facilitators to this behaviour change. In addition, the women's weight gain during pregnancy (women will be weighed at their booking appointment at the end of their pregnancy) and clinical outcome data (e.g. type of birth and blood loss) will be examined. The focus groups will provide follow-up data about the women's views towards the programme after giving birth.

**Table 2 T2:** Data collection and outcome measures

	Recruitment (screening sheet)	Recruitment (baseline)	Start of 10-week programme	End of 10-week programme	10-week programme register	End of pregnancy	Follow-up questionnaire	Follow-up interview/focus group	Diary
Demographics	X								

Physical Activity Readiness Questionnaire (PARQ) - [31]	X	X							

Weight (weight gain during pregnancy and Body Mass Index [BMI])	X					X			

Pregnancy physical activity questionnaire (PPAQ) [49]		X	X	X			X		

Physical activity changes - barriers/facilitators to this change			X	X			X	X	X

Attitudes towards physical activity		X	X	X			X	X	X

Attitudes towards their pregnancy and baby		X	X	X			X	X	X

Food intake changes - barriers/facilitators to this change			X	X			X	X	X

Attitudes towards food intake		X	X	X			X	X	X

General Self-efficacy scale (GSES) [50]		X	X	X			X		

Well-being (W-BQ12) [51]		X	X	X			X		

Attitudes towards their weight			X	X			X		X

Experience of advice received about weight gain during pregnancy	X	X	X	X			X	X	

View of health care and treatment from health care professionals		X	X	X			X	X	X

Views and attitudes towards 10-week programme				X				X	X

Attendance at 10-week programme				X	X			X	X

Outcome expectations of factors influencing pregnancy		X	X	X			X	X	

Outcome expectations of study participation		X					X		

Goal setting			X						

Goal attainment - barriers/facilitators				X			X		X

Clinical outcome data (e.g., mode of birth and blood loss)						X			

To gain a comprehensive view of the programme, qualitative and quantitative data will be combined and interpreted from different vantage points (e.g. demographic differences). Qualitative data will be transcribed verbatim and analysed using an interpretive approach. Thematic analysis will be used as the process organises and minimises the data whilst maintaining the detail as it '...is a method for identifying, analysing and reporting patterns (themes) within data' (p.79 [52]). It can be applied both in a deductive and inductive nature, thus suitable for extracting new themes from the data as required in a feasibility study with little evidence-base. In addition, thematic analysis allows for theme extraction for each woman individually (vertical analysis) and also between groups (e.g. horizontal analysis of subgroups such as demographics or 10-week programme cohort) resulting in rich results.

Quantitative data will be input onto Statistical Package for Social Scientists (SPSS). Much of the quantitative analysis will be descriptive in nature; findings will be displayed as frequencies and Chi-squared analysis used to explore associations in the data. Pre and post programme data will be examined using Chi-squared and t-tests analysis. The necessary data will be collected from all participants (e.g. the 10-week programme cohort and number of sessions attended) to allow for multi-level analysis taking into account the effect of group dynamics if required.

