### Outcomes

The main outcome of interest is pregnancy weight gain. Other important clinical outcomes include birth weight, mode of birth and method of infant feeding at hospital discharge. Important psychological outcomes include self-efficacy, well-being and goal attainment. Secondary outcomes include women's experience of pregnancy and health care services, amount of physical activity, food intake and the suitability of the intervention components.

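### Frequencies and Chi-squared are the only method named for associations, although weight gain, birth weight, the scale scores and attendance are continuous measures or counts

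*Protocol article*

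**What the plan says.** The Outcomes section of the protocol article states: "The main outcome of interest is pregnancy weight gain". It continues: "Other important clinical outcomes include birth weight, mode of birth and method of infant feeding at hospital discharge". Self-efficacy and well-being are listed there as important psychological outcomes. Table 2 shows that they are measured by the GSES and the W-BQ12, and physical activity by the PPAQ.

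The quantitative plan is one paragraph in Data Collection and analysis, with three relevant parts:

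- **Description and associations.** The approach is mainly descriptive, and the method named under it is that "findings will be displayed as frequencies and Chi-squared analysis used to explore associations in the data".
- **Change over the programme.** "Pre and post programme data will be examined using Chi-squared and t-tests analysis".
- **Modelling.** Items such as "the 10-week programme cohort and number of sessions attended" are collected "to allow for multi-level analysis taking into account the effect of group dynamics if required".

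No correlation, regression or between-group comparison of means is named for associations. No cut-point is given for any measure.

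**The concern.** A Chi-squared test of association needs categories. Weight gain and birth weight are continuous, the three questionnaires give scores, and attendance at a 10-week programme is a count. To test any of these against another variable by the named method, someone must choose where to cut.

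The t-test sentence does not cover the main outcome. Table 2 records weight at recruitment and at the end of pregnancy, not at the start and end of the programme, so weight gain is one value per woman. A paired test of end weight against early weight would show only that pregnant women gain weight. Birth weight has no earlier value at all. For questions such as whether weight gain differs by demographic group or attendance, Chi-squared is the only test named.

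Three things are at stake:

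- **Information.** Women on the same side of a cut are treated as alike, so exploratory associations become harder to see.
- **Arbitrariness.** The Background says that there is little UK evidence for the published weight-gain ranges and no UK guideline, so no external cut suggests itself. A cut chosen after looking at the data would raise the false-positive rate.
- **Usefulness for the later trial.** Frequencies with a Chi-squared P value give no effect estimate on the scale of kilograms or score points.

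**Working it through.** **1. The plan's own figure.** Under Sample, 200 participants give 80% power for a standardised pre-post change of 0.2 by paired t-test. The level is not stated; two-sided 5% is assumed.

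- Normal approximation: Φ(0.2 × √200 − 1.96) = Φ(2.828 − 1.96) = Φ(0.868) = 80.7%.
- Noncentral t: 80.4%.

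The stated 80% is reproduced. It concerns the paired test on the original scale, and nothing below changes it.

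**2. Inputs for the illustration.** N = 200 comes from Sample. Two-sided 5%, normal distributions, median splits and the effect sizes are assumptions. The effects are chosen to give about 80% power when nothing is cut.

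**3. One variable cut** (for example, weight gain in two subgroups of 100 that differ by d = 0.4 SD).

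- Original scale: noncentrality 0.4 × √(100 × 100 / 200) = 2.828; t-test power 80.4%.
- Cut at the overall median: proportions above the cut are Φ(−0.2) = 42.1% and Φ(0.2) = 57.9%, a difference of 0.1585. The null standard error is √(2 × 0.25 / 100) = 0.0707. The alternative standard error is √(2 × 0.421 × 0.579 / 100) = 0.0698. Power = Φ((0.1585 − 1.96 × 0.0707) / 0.0698) = Φ(0.285) = 61.2%.
- Loss: 80.4 − 61.2 = 19 points. With a cut that leaves 20% above it, power is 49.5% and the loss 31 points.

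**4. Both variables cut** (two continuous measures correlated at r = 0.2).

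- Original scale (Fisher z): Φ(atanh(0.2) × √197 − 1.96) = Φ(2.846 − 1.96) = 81.2%.
- Both cut at the median: the 2×2 correlation is (2/π) × asin(0.2) = 0.128, so the proportions are 56.4% and 43.6%. Power by the formula in step 3 is 44.1%.
- Loss: 81.2 − 44.1 = 37 points.

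**5. Dependence on the assumed effect (median splits).**

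| One split, d | Loss (points) | Both split, r | Loss (points) |
|---|---|---|---|
| 0.2 | 9 | 0.10 | 15 |
| 0.3 | 17 | 0.15 | 29 |
| 0.4 | 19 | 0.20 | 37 |
| 0.5 | 14 | 0.25 | 32 |
| 0.6 | 7 | 0.30 | 20 |

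**6. Simulation check** (3,000 runs each, cuts at the sample median). One split costs 15 points without continuity correction and 26 with it. Two splits cost 32 and 44. The formula values lie between, for a simple reason. With all margins fixed at 100, the uncorrected statistic is 0.08 × (a − 50)², where a is the count in one cell. It exceeds 3.84 once a is 7 or more from 50, because 0.08 × 49 = 3.92. The standard deviation of a is √(100⁴ / (200² × 199)) = 3.54, so the true level is about 2 × (1 − Φ(6.5/3.54)) = 6.6%. With the correction, a must be at least 8 from 50, and the level is about 2 × (1 − Φ(7.5/3.54)) = 3.4%. One version is slightly liberal and the other conservative.

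**7. How many measures are affected.** Of the 21 rows in Table 2, about five are clearly scores, weights or counts: weight, PPAQ, GSES, W-BQ12 and attendance. Clinical outcome data are mixed. Most of the rest are attitudes, views, barriers, expectations or goals.

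**The case against.** The strongest reply is that nowhere does the article say that weight gain or any score will be cut. The sentence on associations belongs to a general summary of much, not all, of the analysis. T-tests follow in the next sentence. The count of sessions attended is collected with possible multi-level analysis in mind. Under Sample, standard deviations and an intraclass correlation are to be estimated, so measures are clearly expected on their original scale too. The formal comparisons are the pre-post ones, and associations were never powered. In a condensed article, the choice of correlation or regression may have been left to a fuller document.

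Much of this stands, and it limits the point. A reader might infer that the plan reduces all its outcomes to categories, that most of its measures are continuous, or that its 80% power is undermined. None of these is supported. The pre-post analysis can stay on the original scale, most rows of Table 2 may suit frequencies and Chi-squared, and the 80% reproduces. Nor does the article set itself the aim of finding which women or how much attendance go with lower weight gain; the Discussion speaks of acceptability and suitability.

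What does not stand is that this is only an omitted detail. The article names a method for associations, and that method does not fit the main outcome without grouping. The t-test sentence is confined to pre/post data, and the multi-level analysis is conditional and directed at group effects.

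**Conclusion.** The point holds for a limited set of measures: weight gain, birth weight, GSES, W-BQ12, PPAQ and number of sessions attended. For associations involving these, the only named method requires grouping at unstated cut-points, or leaves them untested.

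The losses of about 19 points (one median split) and 37 points (both variables split) illustrate the cost near 80% starting power. They rest on assumed effects, an assumed two-sided 5% level, 200 women with complete data and median cuts. Over the other effects tabulated, the loss is between about 7 and 37 points. They are not a finding about the plan's stated power, which is unaffected. A higher false-positive rate would follow only if cuts were chosen from the data, which the article does not say.

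Because the associations are exploratory and the study is one of feasibility, the consequence is moderate. The change is still worth making, because the main outcome is affected and the cost is close to nil.

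**What to change.** Replace the sentence on associations with wording to this effect: Chi-squared tests will be used for variables that are categorical by nature, such as mode of birth, method of infant feeding and categorical attitude items. Associations involving weight gain, birth weight, questionnaire scores and number of sessions attended will be analysed on their original scale, by linear regression or comparison of means, or by rank correlation if distributions are skewed. Results will be given as estimates with 95% confidence intervals. Any grouping of these measures will be for description only.

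The cost is slightly more analysis work in the same software (SPSS), with no new data and no change to the sample size or to the pre-post analysis.

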## Methods/Design

This is a prospective study, using mixed-methods of data collection to inform the feasibility of implementing a community lifestyle programme with pregnant women with a BMI or 30 kg/m^2 ^or more in the Greater Manchester areas of Bolton and Oldham. Randomised controlled trials are considered the gold standard when assessing interventions [28]. However, one has to be sure that the intervention is of the highest standard, and acceptable to those who will be receiving it prior to proceeding to a randomised controlled trial. There is currently no evidence suggesting the optimum intervention for this group of women, nor is there any evidence of intervention acceptability. Therefore, following the advice of the Medical Research Council (MRC) framework for a complex intervention [29] we believed it imperative that a feasibility study was conducted prior to any such trial. Our approach to programme development is one which allows fluidity, i.e. the programme will be adapted contemporaneously following feedback and review.

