### Sample

Four hundred pregnant women with a BMI of 30 kg/m^2 ^or more will be approached to participate in the study (200 from each area). Women will be excluded from participation in the study if they have a BMI of less than 30 kg/m^2^, are aged under 18, intend to move in the next three months, take weight control medication or if they have any cautions for starting exercise (this will be determined using the Revised Physical Activity Readiness Questionnaire (PARQ) [31]) and the Royal College of Obstetricians and Gynaecologists (RCOG) recommendations [32]). Their obstetrician will be consulted in cases where the PARQ or RCOG guidelines indicate concerns. Each participant's General Practitioner (GP) will be sent a letter outlining the involvement in the study. The sample size is determined pragmatically by the need to gain sufficient experience of the intervention over a range of settings and participants and thus test feasibility on a realistic basis. 200 participants is more than adequate to estimate standard deviations and 10-12 groups will allow us to estimate the intraclass correlation for the design of future studies. Formal comparisons are pre-post measures where 200 participants will give 80% power to detect small changes of 0.2 or larger, expressed as standardised effect sizes in terms of the intra-patient standard deviation (80% power, paired t-test). The major obstetric outcomes (caesarean section and low birth weight) have expected incidence rates of around 20% [6] and will be estimated with a 95% confidence interval width of approximately 5%, allowing large effects to be detected in comparison with audit data.

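### The 80% power and the planned pre-post t-tests treat 200 women as independent although they are taught in 10-12 fixed, interacting groups, and the clustered analysis is only conditional

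*Protocol article*

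**What the plan says.** Under Sample, the protocol article states: "Formal comparisons are pre-post measures where 200 participants will give 80% power to detect small changes of 0.2 or larger". The test named there is a paired t-test, with the effect scaled by a within-woman SD. No allowance for grouping is made. The preceding sentence says that "10-12 groups will allow us to estimate the intraclass correlation for the design of future studies".

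The Theoretical framework section makes the group part of the mechanism: "The women will be in the same group for the whole programme so will gain social support and feedback on their behaviour". Table 1 likewise lists feedback, reinforcement and support from other group members among the behaviour change techniques.

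Under Data Collection and analysis, pre- and post-programme data are to be examined with chi-squared and t-tests. Programme cohort and number of sessions attended are collected from every participant "to allow for multi-level analysis taking into account the effect of group dynamics if required". No criterion is given for when that analysis would be required.

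**The concern.** Women who share an instructor, sessions and peer feedback for ten weeks may change in similar ways. If they do, 200 change scores carry less information than 200 independent ones. An ordinary paired t-test then uses a standard error that is too small, so it rejects too often, and power computed from n = 200 is too high.

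The article treats the ICC as a quantity worth estimating for later studies but in effect sets it to zero in its own power calculation. It also leaves the choice between an unadjusted and a clustered test open until the data are in hand. At stake are the error rate of the comparisons that the article itself calls formal, and the credibility of its power figure.

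**Working it through.** **Inputs from the article.** Sample: n = 200, standardised change 0.2, paired t-test, 80% power, 10-12 groups. Theoretical framework: fixed group membership. Data Collection and analysis: t-tests as the named pre-post analysis.

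**Assumptions, not in the article.** Two-sided 5% test; 0.2 in units of the SD of the change; groups of equal size; paired data from all 200 women; change-score ICC of 0.01, 0.05 or 0.10.

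**Step 1: the plan's own figure.** The noncentrality is 0.2 × √200 = 2.83. The noncentral t with 199 df gives power 80.4%, and 199 women are needed for 80%. The stated figure therefore reproduces, but only with a design effect of exactly 1.

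**Step 2: design effect.** With 11 groups, m = 200/11 = 18.2.
- Design effect: DE = 1 + (m − 1) × ICC, for example 1 + 17.2 × 0.05 = 1.86.
- Effective sample size: 200/DE, for example 200/1.86 = 107.6.
- Type I error of the unadjusted test: 2 × [1 − Φ(1.96/√DE)]. At ICC 0.05, 1.96/√1.86 = 1.44, giving 15%.
- Power: noncentral t with noncentrality 0.2 × √(200/DE), first with 199 df (design effect alone), then with 10 df (11 groups minus 1).

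| Assumed ICC | DE | Effective n | Type I error, unadjusted test | Power, design effect alone | Power, 10 df |
|---|---|---|---|---|---|
| 0 | 1.00 | 200 | 5% | 80% | 72% |
| 0.01 | 1.17 | 171 | 7% | 74% | 65% |
| 0.05 | 1.86 | 108 | 15% | 54% | 47% |
| 0.10 | 2.72 | 74 | 24% | 40% | 34% |

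Simulation of the unadjusted test with 11 groups (20,000 runs) gave type I errors of 6.8%, 14.9% and 23.7% at the three positive ICCs.

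**Step 3: sensitivity to the number of groups.** At ICC 0.05, 10 groups of 20 give DE 1.95 and type I error 16%; 12 groups of 16.7 give DE 1.78 and 14%. The conclusion does not depend on where in 10-12 the number falls.

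**Step 4: sensitivity to group size.** If only 12 women per group gave paired data, DE would be 1 + 11 × ICC = 1.11 / 1.55 / 2.10, so the inflation would be smaller.

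**Step 5: precision of the ICC.** Suppose 11 groups of 18 yield an estimated ICC of 0.05. The F ratio is (1 + 17 × 0.05)/(1 − 0.05) = 1.947, with 10 and 187 df. The F-based 95% limits are −0.004 and 0.220, that is, about 0 to 0.22.

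**The case against.** The strongest reply is that this is a feasibility study. Its size is said to be pragmatic, most of the quantitative analysis is descriptive, and no progression decision hangs on a pre-post p-value. Cohort membership is collected with multi-level analysis in mind, and a condensed article may leave model details to a full protocol or analysis plan. The ICC is assumed: nothing in the article supports 0.05 or 0.10 for change scores, and at 0.01 the inflation is small. This lowers the severity, and the absence of model detail is not itself the fault. It does not remove the point, because the article positively states a power figure, names the test and makes the clustered analysis conditional.

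Some stronger readings are tempting but not supported:
- **That clustering cuts power to 65-34%.** Part of that drop comes from using 10 df; power is already 72% at ICC 0.
- **That too few groups will mis-size the later randomised trial.** The article promises only to estimate the ICC. It claims no precision and does not say that the trial will be sized on the point estimate.
- **That between-group variance is confounded with programme version.** The article says "the programme will be adapted contemporaneously following feedback and review". It defines no discrete versions and does not place changes between cohorts. A fixed effect for version would also use up scarce between-group degrees of freedom.
- **That false-positive changes will be taken for programme effects.** Without a control group, any pre-post change is confounded with advancing pregnancy, and no clustered model cures that.

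**Conclusion.** The concern holds, at moderate severity. The stated 80% power and the named t-tests are correct only if the ICC of the change scores is zero, an assumption that sits badly with an intervention built on group interaction and a stated aim of estimating the ICC. For any positive ICC the direction is certain: p-values too small and power below 80%. The size is not certain. It ranges from minor at ICC 0.01 to serious at 0.10, and rests on assumed ICCs, equal groups and complete pairs. A reader might infer that the article expects a non-zero ICC, or that the error is known to be large; it establishes neither.

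**What to change.** 1. In Data Collection and analysis, remove the condition on the multi-level analysis. Make a cluster-adjusted analysis the default for the formal pre-post comparisons: a model for the change score with a random intercept for programme group and small-sample degrees of freedom.
2. In Sample, restate power for a 0.2 SD change over an explicit, assumed ICC range, and say which degrees of freedom are used. The table above can serve as it stands for 11 groups.
3. Report the estimated ICC with its confidence interval, so that readers see how imprecise an estimate from 10-12 groups is.

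No fixed effect for programme version and no rule for sizing the later trial is needed for this point. The cost is a few sentences and a modest amount of analysis. The group identifier is already collected, and recruitment and programme delivery do not change. The stated power will look less favourable.
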